## Methods

2

### Study Design

2.1

A two‐arm, parallel‐group, randomized, participant‐ and assessor‐blinded controlled trial will be conducted in Bangladesh from November 2025 to April 2026, following the recommendations of the Standard Protocol Items: Recommendations for Interventional Trials (SPIRIT; Figure 1) [22]. Following consent, Randomization will be done among the participants in a ratio of 1:1 by an Excel randomizing procedure to receive either FES with UPT (Experimental group or Group A) or placebo FES with UPT (Control group or Group B) for an 8‐week intervention period. The results will be reported in accordance with the CONSORT (Consolidated Standards of Reporting Trials) guidelines (Figure 2).

**Figure 1 hsr273276-fig-0001:**
[figure not shown]
Timeline of enrollment, assessment, and intervention.

**Figure 2 hsr273276-fig-0002:**
[figure not shown]
CONSORT flow diagram.

### Study Settings

2.2

This study will involve patients from the Neurology unit of the Physiotherapy and Rehabilitation department of Jashore University of Science and Technology in Bangladesh. This study setting is well‐recognized in Bangladesh for its physiotherapy and rehabilitation services.

### Sample Size Calculation

2.3

Sample size calculation is performed using G*Power software version 3.1.9.7 for a two‐tailed independent‐groups test comparing two group means. The effect size (Cohen's *d*) is set to 0.5 (medium effect) based on prior research in post‐stroke rehabilitation [23]. The α value is predetermined as 0.05, and the power (1–β) is 0.80 to limit the risk of Type II error. Based on these parameters, we will need 64 individuals per group, for a total of 128 participants. Finally, we plan to recruit 140 participants (70 per group), allowing for an anticipated dropout rate of approximately 10%.

### Participants' Recruitment Process

2.4

Participant recruitment will begin in November 2025, targeting individuals undergoing post‐stroke rehabilitation who meet predefined inclusion and exclusion criteria. Eligibility assessments will be conducted by trained research assistants who are independent of the rehabilitation process to reduce bias. Each participant will be assigned a unique identifier and coded in an Excel database. Eligible participants will be comprehensively informed of the study's objectives, procedures, risks, and benefits and will provide written informed consent using an institutional ethical review board‐approved form. Then, they will be assigned to a group to receive intervention as per protocol. All study documentation will be securely stored to protect data integrity.

### Randomization and Blinding Procedures

2.5

Following consent, participants will be randomly assigned in a 1:1 ratio to either Group A or Group B using simple randomization performed through Excel's = RAND() function by an independent research assistant not involved in recruitment, treatment, or assessment. Allocation concealment will be ensured using sequentially numbered, opaque, sealed envelopes prepared by an independent assistant. This study will employ participants, and outcome assessors will be blinded to group allocation throughout the study period. Due to the nature of the intervention, treating physiotherapists administering FES cannot be blinded; however, they will not participate in outcome assessment or data analysis. Participants in both groups will receive identical treatment durations, therapist interactions, electrode placement procedures, and device preparation to maintain the credibility of blinding. Outcome assessments and statistical analyses will be conducted by independent personnel blinded to treatment allocation. Participants will also be instructed not to discuss their intervention experiences with assessors to minimize detection bias.

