Despite the widespread use of FES in neurorehabilitation, current evidence regarding its effectiveness in reducing hand pain and improving function in people with stroke remains inconclusive. Several studies have reported improvements in motor performance following FES application; however, considerable variability in intervention protocols, outcome measures, and study populations limits the generalizability of the findings. Moreover, pain is a significant yet often underreported barrier to functional recovery and has not been adequately addressed in most of the FES‐focused trials. Notably, few randomized controlled trials (RCTs) have concurrently examined both pain and hand‐specific functional outcomes following FES in individuals with stroke [21]. Although recent literature encourages the use of FES in upper extremity stroke rehabilitation, its application, especially when combined with well‐structured standard care for post‐stroke hand impairments, remains limited and still unfamiliar in clinical settings. Previous studies have shown mixed results, often hindered by poor methodology, limited outcome measures, and a lack of long‐term follow‐up, leaving their optimal effectiveness uncertain when assessed with robust methodological standards [13, 18].

Therefore, this prospective, randomized controlled trial (RCT) is relevant and aims to complement and contribute to the existing scientific effort by maintaining a strong methodological rigor. The primary objective of this trial is to evaluate the effectiveness of FES‐integrated UPT in reducing hand pain and improving hand function in stroke patients. The secondary objectives are: (1) to evaluate sociodemographic factors such as age, gender, stroke type, and time since stroke that may affect post‐stroke pain and functional recovery; (2) to establish baseline compatibility between the experimental and control groups; (3) to assess changes and compare group differences across all outcome measures at mid and post‐intervention periods; and (4) to explore the long‐term benefits of FES‐integrated UPT in maintaining improvements during the follow‐up period. It is hypothesized that FES‐integrated UPT will result in significantly greater improvements in hand pain, function, muscle tone, and manual dexterity compared to placebo FES with UPT, with these improvements being more long‐lasting.

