### Data Analysis

2.13

All analyses will be conducted by an independent statistician using SPSS version 22 with anonymized, encrypted data. Data will be screened for completeness, missing values, and outliers prior to analysis. Normality will be assessed using the Kolmogorov–Smirnov and Shapiro–Wilk tests, along with measures of skewness and kurtosis, and visual inspection (histograms and *Q*–*Q* plots). Descriptive statistics will be presented as mean ± standard deviation for normally distributed variables, median (interquartile range) for non‐normally distributed variables, and frequency (percentage) for categorical variables. Baseline characteristics (e.g., age, BMI, disease duration) will be compared between the two groups to assess group equivalence. Given the two‐group design (intervention vs control) with four time points (baseline, mid‐intervention, post‐intervention, and follow‐up), a two‐way repeated‐measures ANOVA (group × time) will be used for normally distributed outcomes to evaluate main effects and interaction effects. For non‐normally distributed data, the Friedman test (within‐group) and Mann–Whitney *U* test (between‐group at each time point) will be applied, with appropriate post hoc analyses. Within‐group changes over time will be assessed using repeated‐measures ANOVA (or Friedman test), while between‐group differences at each time point will be examined using independent *t*‐tests (or Mann–Whitney *U* tests). When significant interactions are identified, post hoc pairwise comparisons with appropriate corrections (e.g., Bonferroni) will be performed. Effect sizes (e.g., partial eta squared or Cohen's *d*) and mean differences with 95% confidence intervals will be reported alongside p‐values. All tests will be two‐tailed, with statistical significance set at *p* < 0.05. An intention‐to‐treat (ITT) approach will be applied, and missing data will be handled using the last observation carried forward (LOCF) method. Additionally, change scores across all four time points will be calculated to support the interpretation of clinical relevance.

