## Discussion

3

Despite rehabilitation, many stroke survivors continue to experience upper extremity impairments that significantly affect their activities of daily living (ADLs). This study will examine the application of FES‐integrated UPT to enhance upper‐extremity mobility in individuals who have experienced a stroke, with follow‐up to assess long‐term effectiveness. These findings may contribute to the development of evidence‐based intervention strategies for stroke rehabilitation in Bangladesh and other settings. Consequently, it could have significant implications for rehabilitation practices in low‐ and middle‐income countries. A key strength of the study is its randomized treatment allocation, which minimizes selection bias and strengthens the validity of the results. Stroke patients with severe pain may have impaired hand function. Hand function in stroke patients is linked to discomfort, deficits, and physical function. Pharmaceutical management has limited effects, while non‐pharmacological therapies, including exercise therapy, have short‐term effects in stroke sufferers [37]. This study addresses a research gap by exploring how FES‐integrated exercise treatment improves hand pain and function in stroke survivors, with an emphasis on assessments of improvement with rigorous methodology. Several studies have evaluated the impact of FES on the hand function of stroke patients [38, 39], and most have also been poorly designed and have had inadequate sample sizes. These studies suggest that FES improves hand function. The current research also suggests that further investigation is necessary to determine the long‐term effects of integrating FES with physiotherapy on hand pain and function. Stroke patients with hand disability are treated in institutional care using a safe hand functional rehabilitation strategy [40]. The usual physiotherapy treatment in this study was developed based on consensus guidelines for stroke rehabilitation [41], the national protocol of the Australian Ministry of Health [42], and evidence from high‐quality contemporary stroke literature [43]. These interventions were selected to ensure equal care for both groups. The study will be conducted at a renowned Bangladeshi physiotherapy and rehabilitation facility that uses evidence‐based therapeutic protocols. It aims to evaluate the comparative effectiveness of FES combined with usual physiotherapy treatment versus placebo FES with usual physiotherapy in improving hand pain and upper extremity function among stroke survivors. Following the intervention, all participants will receive free exercise guidance, and the study will adhere to SPIRIT and CONSORT standards, incorporating appropriate blinding and masking. The study will employ valid and reliable outcome measures and implement procedures to prevent cross‐contamination of data. Since the questionnaire is not available in Bengali, the study used standard translation. The project will also train trial stakeholders. Despite its complexity, the study process is meticulously designed, synchronized, and purposeful. This study will briefly discuss the paradigm shift in stroke treatment and the prospective use of FES. This study's strengths include addressing a recognized research gap, adherence to established protocols and guidelines, and careful planning to ensure an adequate sample size, calculated using G*Power to achieve sufficient statistical power. Simple random sampling ensured unbiased group allocation, valid outcome measures will be used, and rigorous blinding and masking procedures will be applied to maintain methodological rigor. This study may have some limitations, including its exclusive focus on Bangladesh, variability in patients' comorbidities, diversity in patients' clinical conditions and stroke severity, and a broad age range, which may affect the overall findings. Despite these constraints, the findings from the rigorously designed randomized controlled trial will provide valuable insights into stroke rehabilitation. Future research may investigate the effectiveness of FES compared with no electrical stimulation, or when combined with more specific or structured rehabilitation programs, using larger sample sizes and longer follow‐up periods.

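### Simple randomisation will rarely give the stated 70/70 arms and leaves chance imbalance in initial severity uncontrolled, with no severity covariate named

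*Protocol article*

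**What the plan says.** **Allocation.** Section 2.5 of the protocol article states that "participants will be randomly assigned in a 1:1 ratio to either Group A or Group B using simple randomization performed through" Excel's RAND function, run by an independent assistant and concealed in numbered sealed envelopes. Section 2.1 describes allocation "in a ratio of 1:1 by an Excel randomizing procedure". Neither section mentions blocks or strata.

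**Arm sizes.** The abstract gives 70 in each group. Section 2.3 says "we will need 64 individuals per group, for a total of 128 participants", and then "we plan to recruit 140 participants (70 per group), allowing for an anticipated dropout rate of approximately 10" per cent.

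**Severity and balance.** The Introduction reports a poor outlook for hand dexterity when the Fugl-Meyer upper-extremity score is very low two weeks after stroke. It also makes baseline comparability "between the experimental and control groups" a secondary objective. Eligibility admits Brunnstrom stage 3 or less. The Discussion lists variation in stroke severity as a limitation.

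**Analysis.** Section 2.13 compares baseline characteristics between groups and uses a group-by-time repeated-measures ANOVA. It tests the groups against each other at each time point with independent t-tests or Mann–Whitney tests. Change scores are calculated as support. No covariate is named.

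**The concern.** Two things do not fit together.

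1. Simple randomisation lets arm sizes vary, yet the plan states fixed arms. One of the two descriptions has to change.
2. The plan treats initial severity and baseline comparability as important, but nothing in the allocation or the named analysis acts on them. Comparing groups at baseline can reveal an imbalance but cannot correct it.

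At stake is precision and a clear reading of the result, not validity. If the arms happen to differ in initial severity, the unadjusted comparisons at weeks 4, 8 and 20 will carry part of that difference, and readers will be unsure how much of any FMA-UE effect it explains.

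**Working it through.** **Inputs from the article.** N = 140, stated as 70 + 70; 64 per group needed; d = 0.5; power 0.80; "The α value is predetermined as 0.05", two-tailed. **Assumptions, not in the article:** a binary severity factor present in 30% to 50% of patients; block sizes 4 and 6; a baseline-to-outcome correlation of 0.7 to 0.9.

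**1. The plan's own figure.** For a two-sample t-test, df = n1 + n2 − 2 and the noncentrality is d·√(n1·n2/(n1 + n2)). This gives 80.1% power at 64 per group and 79.5% at 63, so the stated 64 reproduces.

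**2. Arm sizes under simple randomisation.** The size X of one arm is Binomial(140, 0.5), with SD √(140 × 0.25) = 5.9.
- P(X = 70) = C(140, 70)/2^140 = 6.7%
- Mean |2X − 140| = 9.4
- Central 95% range: 58 to 82
- P(75/65 or worse) = 44.7%; P(80/60 or worse) = 10.8%

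**3. What unequal arms cost in power.** At 70/70 the noncentrality is 0.5 × √35 = 2.96. At 82/58 it is 0.5 × √(82 × 58/140) = 2.91.

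| Split of 140 | Power, all 140 evaluable | Power, 128 evaluable in the same ratio |
|---|---|---|
| 70/70 | 83.6% | 80.1% |
| 80/60 | 82.8% | 79.3% |
| 82/58 | 82.5% | 79.0% |

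Averaged over the binomial distribution, power is 83.3% at N = 140, a loss of about 0.3 points.

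**4. Chance imbalance in severity.** The SD of a standardised baseline difference is 2/√140 = 0.169. Then 0.2/0.169 = 1.18, and P(|difference| ≥ 0.2 SD) = 23.7%. For 0.25 SD the chance is 13.9%.

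Simulation of the binary severity factor (8,000 runs per setting, prevalence 30% and 50%):

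| Allocation | Imbalance of 10 points or more | Exactly equal arms |
|---|---|---|
| Simple | 19% and 24% | about 7% |
| Fixed 70/70 list, no strata | 22% and 23% | 100% |
| Stratified blocks of 4 and 6 | about 0% | about 55% |

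With stratified blocks the arms differed by at most 2 in about 95% of runs, and by 4 to 6 at most. A fixed list settles the arm sizes but does nothing for severity.

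**5. What a 0.2 SD baseline gap does.** With a baseline-to-outcome correlation of 0.7 to 0.9 and equal SDs:
- Unadjusted comparison at a later visit: 0.2 × 0.7 = 0.14 SD to 0.2 × 0.9 = 0.18 SD, which is 28% to 36% of the design effect of 0.5.
- Change from baseline: 0.2 × (0.7 − 1) = −0.06 SD to 0.2 × (0.9 − 1) = −0.02 SD.

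**The case against.** The best defence is that simple randomisation of 140 patients is a valid, conventional method. It balances severity in expectation, and standard errors and type I error already allow for chance imbalance. All of that stands. A reader might infer that the allocation is biased or that the arms will be unbalanced in severity. The article does not support either: when the Discussion says "Simple random sampling ensured unbiased group allocation", the word sampling is loose, but the claim of no bias is correct.

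A reader might also note that the smaller arm falls below 64, before any dropout, in 27% of cases and infer an underpowered trial. That does not follow. Power depends on both arms together, and the table above shows a loss of about one point even at 82/58.

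The group-by-time interaction and the change scores work on change from baseline, so a baseline gap in the same score is largely removed there, as step 5 shows. This stands in part. The t-tests at each time point remain unadjusted. The change-score result also supposes that gain does not depend on severity, which the Introduction's remark on very low scores calls into question. That remark concerns scores at two weeks, whereas patients enter at one to three months, so it is indicative only.

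Naming a covariate would deal with much of this without touching the allocation. That also stands, and it is why the fix includes the model.

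Finally, RAND takes no seed and recalculates, so a reader might infer that the list cannot be audited. The article does not say that a live sheet will be used, and envelopes fix the sequence once prepared. Archiving the list is a detail that an article commonly leaves to the full protocol, so this is not a fault.

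**Conclusion.** The point holds in a limited form. As written, the allocation method and the stated arm sizes disagree: 70/70 would arise in about 7% of cases. The text must say whether RAND assigns each patient or sorts a fixed list. This is a matter of consistency, with a negligible effect on power.

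The more useful point is that chance imbalance in initial severity is left uncontrolled, with about a 24% chance of 0.2 SD or more on a given score. That risk comes from neither stratifying nor adjusting; it does not come from RAND or from unequal arms. The 24% needs only N = 140 in roughly equal arms. The size of the carry-over into unadjusted tests rests on the assumed correlation, and the simulated gain rests on the assumed prevalence and block sizes.

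This is a worthwhile improvement, between optional and recommended, and not a threat to validity.

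**What to change.** **Section 2.5.** Before recruitment (section 2.16 says that none has taken place), replace simple randomisation with permuted blocks of randomly varying size, for example 4 and 6, stratified by baseline Brunnstrom stage (1–2 versus 3). The stage is already assessed for eligibility, and section 2.11 places baseline data collection before allocation. Keep the independent assistant and the sealed envelopes, with one envelope series per stratum, and do not disclose the block sizes.

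**Section 2.13.** Include the stratum and the baseline value of the outcome in the primary model.

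**Abstract and section 2.3.** Describe 70 per group as the target under 1:1 allocation. If a sorted list of 70 A and 70 B was intended all along, say so and drop the word simple; the severity point would remain.

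Do not add hand pain as a second stratum. The Introduction's figure of 4.6% would mean about 0.046 × 140 = 6 patients if it applied here (the trial's own rate is not given), too few to fill blocks.

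**Cost.** A new list, a second envelope series and a few sentences of text. The real trade-off is that blocks are slightly more predictable than simple randomisation at a single site where the treating therapists are unblinded. Varying, undisclosed block sizes limit this. Arms will be nearly equal but not always exactly 70/70.

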### Eligibiity Critetia

2.6

#### Inclusion Criteria

2.6.1

Participants must meet all of the following to be eligible for the study: (1) Confirm diagnosis of unilateral ischemic stroke verified by CT or magnetic resonance imaging (MRI) by a neurologist [24]; (2) Age between 40 and 70 years; (3) Stable vital signs with normal levels of consciousness; (4) Brunnstrom recovery stage between 3 or less for the affected upper extremity function [25, 26]; (5) Presence of mild‐to‐moderate spasticity in the affected upper extremity, based on Modified Ashworth Scale (MAS) score of 1 to 2 in the wrist flexor muscles; (6) Stroke onset between 1 and 3 months before enrollment [27]; (7) Willingness and ability to provide informed consent to participate in the study.

#### Exclusion Criteria

2.6.2

Participants will be excluded if they: (1) Have a previous history of stroke, including reversible ischemic or hemorrhagic stroke; (2) Exhibit severe cognitive impairments or significant speech and communication difficulties; (3) Have a diagnosis of any mental health disorders (e.g., schizophrenia); (4) Have an implanted cardiac pacemaker [28].

### Interventions

2.7

#### Group A (FES‐Integrated UPT)

2.7.1

This group will undergo treatment consisting of 30 min of FES and 30 min of UPT for 8 weeks, three times weekly. The intervention frequency of three sessions per week was selected based on previous upper‐extremity FES rehabilitation studies demonstrating functional improvements with similar training schedules [18]. Training will be provided to the physiotherapists on the FES application before the intervention begins. The XFT‐2003EA H_2_ Hand Rehab System device will be used to deliver electrical stimulations, which can be driven up to 60 mA amplitude, pulse width 250 µs, pulse frequency 40 Hz [29], to the target wrist extensor muscles according to the individual's tolerance. Participants and caregivers will be given a standard warning about the use of electrical stimulation, including watching for signs of skin burns. The electrodes of FES will be placed on the extensor carpi radialis longus and brevis, and the extensor carpi ulnaris [30]. FES will involve performing wrist extension–facilitated functional activities such as Cylindrical, Spherical, Hook, Pinch, and Thumb Adduction, focusing on power and precision. These tasks were selected because effective wrist extension is biomechanically essential for optimizing finger flexor length‐tension relationships, improving grasp stability, and facilitating functional hand use during upper‐extremity activities.

The UPT will be divided into two equal parts: (1) Spasticity management (15 min), involving passive range‐of‐motion (PROM) exercises to replicate joint movements and elongate muscles and soft tissues in segments without active movement, along with sensory stimulation techniques such as brushing and icing to modulate spasticity of the affected wrist joint during wrist flexion, extension, and rotation. (2) Active/functional upper extremity training (15 min), including hand opening/closing, gripping practice, and wrist extension/flexion tasks, with therapist‐assisted facilitation when residual movement is present, followed by relaxation techniques. All exercises will be performed at a moderate intensity (targeting 10–15 repetitions per task, adjusted to patient tolerance) to promote neuromuscular engagement and prevent fatigue [8, 9, 27]. Each session will combine FES and UPT, and each participant will receive a total of 24 treatment sessions.

